## Methods

### Aim and research question

This project aims at developing an Internet-based treatment for BED based on evidence-based CBT [39].

The primary goal is to test the feasibility and suitability of the program and to evaluate the treatment outcome (short-term and long-term) in comparison to a pure and a placebo-inspired waitlist control group (CG) (i.e. reduction of binge-eating episodes and ED pathology as primary outcome variables). We expect that the immediate treatment group (TG) shows a significantly larger improvement in treatment outcomes during the first four weeks of treatment compared to the combined pure and placebo-inspired CGs during the first four weeks of the waiting period. We further expect that all three groups exhibit comparable temporal courses of treatment outcomes in the short (during eight weeks of active treatment) and long term (during the six months of follow-up). Thus, we expect that the placebo-inspired CG shows no advantage in terms of treatment outcome compared to the pure CG and the TG during the treatment and/or the follow-up phase. Our secondary goal deals with moderators and mediators of treatment outcome such as commitment, emotion and impulse regulation capacities, body image or interpersonal problems, depressive symptoms, and level of functioning.

The third goal of this study is to indirectly compare the present Internet-based treatment data with available data from: (1) a face-to-face therapy (group and single setting) in which the same therapeutic approach has been applied [12, 14]; and (2) from a conventional GSH program with a book relying on the same therapeutic concept [38].

The fourth goal is to explore the usability and acceptance of the program in order to gain information about users’ needs and specificities to improve interfaces of Internet-based treatments for vulnerable user groups such as patients with a mental disorder. We evaluate treatment integrity of therapists and treatment adherence of patients in order to increase the internal validity of our findings. The contents of the written feedback of the therapists are evaluated and we rate their fidelity with treatment guidelines. Patients’ compliance with the treatment is assessed using measures such as the time they spent with the program and by the number of exercises which are edited according to treatment suggestions.

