### Statistical analysis

In model 1 we test whether treatment outcomes improve during the active treatment phase across (i.e. pooled for) all three groups to test for the overall efficacy of the GSH program. This model thus contains one within-subjects factor (pre-post). In model 2 we test whether the temporal course of GSH program’s outcomes during active treatment and during follow-up varied among the three groups (TG, CG1, and CG2). We will apply a two-way mixed analysis of variance with group (three levels) as between-subjects and time (pre-post or post-follow-up) as within-subjects factors, whereby we are interested in the interaction between group and time.

Power analyses: based on prior research data (e.g. [25]), we expect an 18% dropout rate for our power estimations. The correlation (rho) of the number of weekly binges between the two time points is estimated to be around 0.6 (using data published in [14]). Here we assume a slightly more conservative value of rho = 0.5. Based on alpha = 0.05 (two-sided), beta = 0.2, a medium effect size (Cohen’s f = 0.25), and a dropout rate of 18%, the estimated sample size is 34 based on model 1 and 42 (14 per group) based on model 2. Taking the larger of these two values (42) this value was subsequently increased to 60 (20 per group) to be on the safe side with respect to the required sample size.

Analyses based on the secondary goal will include moderators and mediator models.

Analyses for the third (compare the present Internet-based treatment with available data from a face-to-face therapy and conventional GSH program with a book) and fourth goal (explore usability) are of exploratory nature and will thus use descriptive statistics such as means, standard deviations, and percentages.

Multilevel models will be used to analyze the data of the first and second goals [50], including multilevel structural equation models (for mediator models in second goal [51]).

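### The expectation of comparable courses and no placebo advantage is paired only with a difference test, so a non-significant interaction cannot support it

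*Protocol article*

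**What the plan says.** Under *Aim and research question*, the article's first efficacy expectation is that immediate treatment beats the two combined waitlist groups over four weeks. The second is one of sameness: "We further expect that all three groups exhibit comparable temporal courses of treatment outcomes", covering the eight weeks of active treatment and the six months of follow-up. From this it infers: "Thus, we expect that the placebo-inspired CG shows no advantage in terms of treatment outcome compared to the pure CG and the TG".

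Under *Statistical analysis*, the matching analysis is model 2: "In model 2 we test whether the temporal course of GSH program’s outcomes during active treatment and during follow-up varied among the three groups". It is a mixed analysis of variance with three groups and two time points, "whereby we are interested in the interaction between group and time". A closing sentence says that multilevel models will be used for the first and second goals.

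The sample size rests on two-sided alpha 0.05, beta 0.2, Cohen's f = 0.25 and a pre-post correlation: "Here we assume a slightly more conservative value of rho = 0.5". The result is that "the estimated sample size is 34 based on model 1 and 42 (14 per group) based on model 2", raised to 60 (20 per group).

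**The concern.** The stated expectation and the stated test point in opposite directions. A test of whether courses vary can reject equality. When it does not reject, the data are compatible with equality and also with every difference inside the confidence interval. The article names no margin, no interval criterion and no other route by which comparable courses or no advantage could be shown. Moving from analysis of variance to multilevel models changes the estimation, not the direction of the hypothesis.

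What is at stake is the conclusion about the placebo-inspired waiting period, which the article presents as new in this disorder. The *Discussion* also considers the opposite outcome, a faster improvement in that group, and calls it relevant for practice. If the test has little power for moderate differences, a null result is likely even when such an advantage exists, and it would look like confirmation of the expectation in the aims.

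**Working it through.** **Inputs.** From *Statistical analysis*: alpha 0.05, power 0.80, f = 0.25, rho = 0.5 (0.6 estimated from earlier data), dropout 18%, N = 42 for model 2, 60 enrolled. Completers: 60 × 0.82 = 49.2, so about 49, or 16 per group. Assumed, because the documents give no relevant difference: true differences in change of 0.5 and 0.8 SD. SD means the outcome SD at one time point.

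**1. The plan's figures.** Noncentral F with k = 3 groups, m = 2 times and λ = f²·N·m/(1 − rho).
- Model 2, N = 42: λ = 0.0625 × 42 × 2/0.5 = 10.5, df (2, 39), power 0.803; N = 41 gives 0.792.
- Model 1, N = 34: df (1, 33), power 0.808; N = 33 gives 0.795.

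Both stated sizes are reproduced, so this is the convention in use. Without the factor m/(1 − rho), model 2 would need 159. The 42 is the size before dropout (42/0.82 gives 52); 60 covers that.

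**2. f in SD units.** With two times, f equals the SD of the three group mean changes divided by 2 SD, so f = 0.25 means that those mean changes have an SD of 0.5.
- One arm departs by δ: SD of means = δ·√2/3, so δ = 0.5/0.471 = 1.06.
- Evenly spaced arms with range δ: SD of means = δ·√(2/3)/2, so δ = 0.5/0.408 = 1.22.

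**3. The trial as enrolled.** Difference in change detectable with 80% power, from one arm departing to evenly spaced arms:

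| Analysed | rho = 0.5 | rho = 0.6 |
|---|---|---|
| 49 | 0.97–1.12 SD | 0.87–1.00 SD |
| 60 | 0.87–1.01 SD | 0.78–0.90 SD |

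**4. Power for assumed differences.** For δ = 0.5, f = 0.118 (one arm departs) or 0.102 (evenly spaced); for δ = 0.8, f = 0.189 or 0.163. Power, evenly spaced to one arm departing:

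| True difference | Analysed | rho = 0.5 | rho = 0.6 |
|---|---|---|---|
| 0.5 SD | 49 | 0.22–0.28 | 0.26–0.34 |
| 0.5 SD | 60 | 0.26–0.34 | 0.32–0.41 |
| 0.8 SD | 49 | 0.49–0.62 | 0.59–0.73 |
| 0.8 SD | 60 | 0.59–0.72 | 0.69–0.82 |

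**5. Interval width.** SD of change = √(2(1 − rho)), which is 1.00 at rho = 0.5 and 0.89 at rho = 0.6. The half-width of a pairwise interval is t × SD of change × √(2/n), with 2n − 2 df.
- n = 16, rho = 0.5: 95% half-width 2.042 × 0.354 = 0.72; 90% half-width 1.697 × 0.354 = 0.60.
- n = 20, rho = 0.5: 2.024 × 0.316 = 0.64; 1.686 × 0.316 = 0.53.
- n = 16, rho = 0.6: 0.65 and 0.54.
- n = 20, rho = 0.6: 0.57 and 0.48.

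Pooling the variance over three groups narrows these by about 0.01 SD.

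**The case against.** The strongest reply is that the article attaches no decision rule to a null result. It states an expectation, says that the interaction is tested, and in the *Discussion* interprets only a positive finding for the placebo-inspired group. The *Abstract* calls the placebo question preliminary, and the full protocol and any analysis plan are not shown. This stands in part: a reader might infer that p > 0.05 will be reported as comparability, but the document does not say so. It does not remove the point, because the article itself fixes the expectation, within its primary-goal paragraph, and the only test tied to it, and the two do not match.

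Four further limits are accepted.
- The 1.06 SD belongs to 42 patients. It should not be quoted as what a trial of 60 can detect.
- The 0.5 SD benchmark is an assumption. A reader might conclude that any relevant difference would most likely be missed. At 0.8 SD that is not so: power is 0.49 to 0.72 at rho = 0.5 and up to 0.82 at rho = 0.6.
- A reader might also infer that equivalence within 0.5 SD could never be shown. At planning values that is true for rho = 0.5, and for rho = 0.6 with 16 per arm. With rho = 0.6 and 20 per arm the 90% half-width is 0.48 SD, so it is possible, though only for an observed difference very near zero.
- Calling f = 0.25 medium is no error. It is labelled as Cohen's f and the sample size follows from it.

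Finally, these figures assume the two-time-point analysis of variance used for planning. Multilevel models with weekly binge counts may be somewhat more precise; the article does not allow a figure for this.

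**Conclusion.** The point holds in a limited form. The expectation of comparable courses and no placebo advantage is paired only with a difference test and has no criterion for sameness, so a non-significant interaction could not support it. On the two-time-point planning assumptions, the trial as enrolled detects differences in change of about 0.9 to 1.1 SD with 80% power at rho = 0.5 (0.78 to 1.00 SD at rho = 0.6). Its pairwise 95% intervals extend 0.64 to 0.72 SD either side (0.57 to 0.65 SD at rho = 0.6). Power is low for an assumed 0.5 SD difference and moderate for 0.8 SD.

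The documents do not show that the investigators intend to read a null as comparability. The four-week comparison of immediate treatment with the combined waitlist groups is not affected.

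**What to change.** - Report the three pairwise differences in change (placebo-inspired minus pure waitlist, placebo-inspired minus immediate treatment, pure waitlist minus immediate treatment) with 95% confidence intervals, as estimation.
- State that a non-significant interaction will not be reported as comparability or as absence of an advantage.
- Claim comparability only if the 90% interval lies inside a margin stated and justified beforehand.
- If the effect size for model 2 is given in SD units, use the value for the planned 60 (about 0.9 to 1.1 SD), not 1.06 SD.
- Reconcile the aims and the *Discussion* on what is expected of the placebo-inspired group.

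This needs no extra patients or data, only wording and a short reporting rule. The cost is a weaker conclusion about the placebo-inspired group: with intervals this wide, the likely report is an estimate with its uncertainty rather than a statement that the groups are alike.

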### Development of the program

When developing an Internet-based GSH program, it is vital to provide a system with a good usability that supports commitment and motivation. This means users should be able to operate the GSH program as easily and intuitively as possible so they can focus on the content of the GSH program and do not need to spend time and effort to figure out how to operate the system. Moreover, it is important that users understand the content and instructions of the GSH program by themselves, with minimal assistance from a therapist. These circumstances impose several requirements in the form and content of a treatment as well as for the interaction design of the user interface of the GSH program. Since Internet-based treatments of mental disorders are quite novel, only little research exists on how usability affects users of such a program (e.g. outcome of a treatment, dropout rate, satisfaction with the treatment). The study by Currie et al. [40] is one of the few examples that took usability into account during the development of an Internet-based CBT program designed to reduce symptoms of emotional distress in students. Three cycles of usability testing including feedback from participants as well as from the counselling center staff lead to both structural (e.g. shortening sections) and stylistic (e.g. aesthetic features) changes, which resulted in a user-friendly platform [40].

To provide the best possible user experience, we aimed to develop a user-friendly Internet-based GSH program that is tailored to the needs of its end-user (in our case BED patients). To do so, the development of our program was driven by a user-centered design (UCD) approach. This means that during the entire development process we laid the focus on the needs, requirements, and limitations of our users. This was done through interviews, low-fidelity prototypes, observation of task-based walk-throughs, and think-aloud usability testing performed by users on functional prototypes. This allowed us to adapt the interface to our users, thereby ensuring a high usability [41].

We decided to apply Garrett’s [42] UCD model (elements of user experience) as a framework to guide the development process and to organize our project phases [43]. Following this procedure led to a fully developed and functional prototype/concept, which was subsequently programmed, evaluated and used to treat BED patients. We conducted extensive end-users research by reviewing literature on the clinical picture of BED, interviewing psychotherapists specialized on the treatment of BED, examining video footage of BED therapy sessions, and surveying *N* = 53 participants with a clinically relevant BED diagnosis (based on Eating Disorder Examination, EDE-Q scores) [44]. The information was used to develop three different personas (i.e. user archetypes used to help guide decisions about the design and features of the GHS program) [45] and to generate usage scenarios to specify the basic functionalities and content requirements of our tool.

### Sample and recruitment

Sixty participants with the primary diagnosis of a BED, that satisfy our inclusion criteria and aged 18–70 years, are randomly allocated (permuted block design; [46]) to three groups: 20 participants will be assigned to the treatment group (TG); 20 participants to a pure waitlist control group (CG 1); and 20 to the placebo-inspired waitlist control group (CG 2). No blinding procedure is applied; allocation is done by one of the primary authors (AW). All patients are required to give informed consent about the study’s procedure (e.g. diagnostic interview and questionnaires pre, post, and follow-up) and commit to follow the contents and guidance during the Internet-based sessions. The only exclusion criteria are pregnancy, the presence of another serious psychological or medical condition that warrants priority treatment, current drug or alcohol abuse, and the lack of sufficient German language or technical skills to work with the program (both self-reported). Recruitment of participants will be promoted via public advertisements and media as well as via cooperating clinical experts. The schedule (SPIRIT) of the trial is presented Fig. 1.

**Fig. 1 Fig1:**
[figure not shown]
Interventional trials (SPIRIT) figure - schedule of enrolment, interventions, and assessments

### Procedure

Altogether the active treatment phase including pre and post-diagnostic lasts approximately 11 weeks (plus four weeks in the control groups). The three follow-up sessions take place one, three, and six months after the last session of the active treatment. All exercises are an integral part of the sessions and mandatory. The patients are invited to work on the different exercises on an individual basis also between sessions.

Each patient is accompanied and guided by one of seven therapists that received a specific training in delivery of the current Internet-based treatment. All therapists are postgraduate psychologists or psychotherapists at the Center for Psychotherapy at the University of Fribourg and are continuously supervised by the study leaders (SM, AW). The therapists provide a weekly written feedback on the exercises via a communication system that is built into the GSH program. Patients can proceed to the next session after completing all parts of the current session along with the related exercises. The next session will then be unlocked for the patient. After finishing a session, patients will have to wait 7–10 days before they can proceed with the next session.

Since dropouts are a major problem in Internet-based treatments for EDs (up to 77%), our GSH program features several measures to support the compliance: a continuous personal contact to a therapist (face-to-face or telephone diagnostic assessment at the beginning of the program and messaging through the build-in communication system during the following three days after each session’s completion); a clear structure of the program (which has been shown to be beneficial in BED self-help programs) (e.g. [23]); and a conjoint scheduling. In addition, the introductory session provides patients with all necessary information to work smoothly through the program. Finally, the first two sessions include several interventions to develop and maintain sustained motivation. Altogether, this procedure aims at supporting the working alliance which has been positively related with the outcome in Internet-based treatments for BED [47].

The therapists that accompany the patients during the GSH program will be trained to provide feedback according to standardized topics and text passages, based on a previous book and email-based BED treatment approach of the outpatient clinic of the research group [38]. These topics are then customized to the patient’s individual needs. The communication between therapists and patients via the built-in communication system will be continuously supervised by the first two authors (SM, AW). Treatment integrity of randomly selected communication (i.e. written contact between therapist and patients) will be evaluated by independent raters according to the previously applied procedures in face-to-face treatments of the group [14, 15].

### Control groups (CG)

After having given informed consent, patients are randomly assigned to the TG (immediate start with the treatment) or either of the CGs. The waiting time in CG 1 (pure waitlist group) and CG 2 (placebo-inspired waitlist group) lasts four weeks. CG 2 will receive standardized weekly messages during their four-week waiting period. These messages include induction of positive expectations regarding program participation, a summary of the current evidence of BED treatment and benefits of such a standardized, evaluated treatment, quotes from former patients, and motivating words. This information does not contain any form of deception. The pure waitlist group will wait exclusively for four weeks. Both CGs fill in a short questionnaire to assess core BED symptomatology (i.e. binge-eating episodes) and to monitor changes in mood. After the waiting period, patients of both CGs start with the Internet-based GSH program.

### Material and measures

The content of the eight sessions and three follow-up sessions is all derived from established and evaluated treatment material [12–15, 39, 48, 49].

In Table 1, an overview of the main contents of each session is given.

**Table 1 Tab1:** Main content of therapy sessions

Session	Content
0	Introduction to the program
1	Individual etiological model of BED
	Self-observation of eating behavior
2	Motivation
	Goal attainment scale
3	Regular eating
	Analyzing binge-eating episodes with the ABC-model
4	Developing strategies to overcome binge-eating (trigger and reaction control)
5	Positive/enjoyable activities
	Working with emergency cards
6	Expanding strategies
	Dysfunctional thoughts
7	Dysfunctional thoughts and body image
	Reduction of overweight
8	Setting longer-term goals
	Coping with future difficulties
	Relapse prevention
Follow-up sessions 1–3	Further goals
	Coping with current difficulties
	Relapse prevention

Table 2 gives an overview of all instruments that will be applied during the study. Primary outcome variables are number of binge-eating episodes and ED pathology. Secondary outcome variables are reduction of depressive symptoms and increase of the level of functioning. Moreover, all exercises that the patients edited during the sessions as well as all communication between the therapist and the patients will be stored and evaluated (e.g. regarding treatment integrity).

**Table 2 Tab2:** Instruments

Instrument	Description/Construct	Time point
Interviews		
Diagnostic interview for psychiatric disorders, short version (Mini-DIPS; [53])	Structured interview to assess psychiatric disorders according DSM-5. Duration: approx. 45 min.	t_1_, t_2_
Eating Disorder Examination (EDE; German version [54])	Structured interview to assess eating disorder pathology Duration: approx. 45 min.	t_1_
Therapists ratings		
Clinical global impression scale [55]	Measure of symptom severity, treatment response and the efficacy of treatments in patients with mental disorders. 7 items rated by the clinician.	t_1_, t_2_
Self-report questionnaires		
Sociodemographic questions (own items)	Sociodemographic questions (gender, age, nationality, sick leave days, prior treatments etc.). 35 items.	t_1_
Patient’s expectancies regarding the therapy (own items)	Questions to assess attitude and expectations of the patients towards the internet-based treatment. 5 items.	t_1_
Work and Social Adjustment Scale (WSAS; [56])	Questionnaire to assess functional impairment (in the area of work, family and social functioning). 5 items.	t_1_, t_2,_ t_3_
Rosenberg Self-Esteem Scale (RSES; [57]	Measurement of self-esteem. 10 items.	t_1_, t_2,_ t_3_
Ein Messinstrument zur Erfassung subjektiver Kompetenzerwartungen (ASKU; [58])	Assessment of subjective expectation of competency. 3 Items.	t_1_, t_2,_ t_3_
Sensitivity to Rejection Scale (MSR; [59])	Scale to measure sensitivity to rejection, submissiveness and ability to deal with threat and hostility. 9 items.	t_1_
Beck Depression Inventory II (BDI-II; German version [60])	Measure of the severity of depressive symptoms. 21 items.	t_1_, t_2,_ t_3_
Beck Depression Inventory Fast Screening (BDI-FS; [61])	Short assessment of depressive symptoms (excluding somatic symptoms). 7 items.	Weekly during waiting time and treatment
Beck Anxiety Inventory (BAI; German version [62])	Measures of the severity of anxiety symptoms. 21 items.	t_1_, t_2,_ t_3_
Eating Disorder Examination-Questionnaire (EDE-Q; German version [63])	Assessment of eating disorders pathology during the past 28 days. 4 scales: eating concerns, weight concerns, restraint eating, shape concerns. 28 items.	t_1_, t_2,_ t_3_
Dutch Eating Behavior Questionnaire (DEBQ; German version [64])	Questions to assess emotional eating. 10 items.	t_1_, t_2,_ t_3_
Weekly Binges Questionnaire (WBQ; [12])	Questions to assess frequency of binge-eating episodes and regularity of eating behavior. 7 items.	Weekly during waiting time and treatment
Thought-Shape Fusion Questionnaire (TSF; [65])	Assessment of body-related cognitive distortions triggered by fattening/forbidden foods. 17 items.	t_1_, t_2,_ t_3_
Food Craving Questionnaire (FCQ trait, short version; [66])	Measure of the intensity of food cravings on a multidimensional level. 15 items.	t_1_, t_2,_ t_3_
Difficulties in Emotion Regulation Scale (DERS; German version [67])	Assessment of central aspects of affective experiences and emotion processing. 36 items.	t_1_, t_2,_ t_3_
Negative Effects Questionnaire (NEQ; [68])	Questionnaire to assess potentially adverse and unwanted events in psychological treatments. 32 items.	t_2,_ t_3_
Adapted version of the Working Alliance Inventory (WAI-SR; [69])	Assessment of main aspects of therapeutic alliance, resource activation, problem actualization, session outcome. 23 items.	Weekly during treatment
Final evaluation of the internet-based treatment (own items)	Assessment of self-reported estimation of therapy outcome. 9 items.	t_2,_ t_3_
Usability		
System Usability Scale (SUS; [70])	10 items to assess usability and user friendliness.	t_2_
Appreciation [71]	Three-item scale to assess to what extent the media experience was considered meaningful, thought-provoking, and moving.	Weekly during treatment
Emotional Engagement with Character [72]	Four-item subscale to assess emotional engagement with a character; used to measure the engagement with the character of a fictional former patient, whose presence guided the patient through the Internet-based treatment sessions.	t_2_

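### Eating-disorder pathology, one of two primary outcomes, has no scheduled measurement at week 4, so the four-week treatment-versus-waitlist hypothesis can be tested only on binge episodes

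*Protocol article*

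**What the plan says.** All references are to the protocol article.

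- **Outcomes** (Material and measures): "Primary outcome variables are number of binge-eating episodes and ED pathology".
- **First hypothesis** (Aim and research question): TG will show a "significantly larger improvement in treatment outcomes during the first four weeks of treatment compared to the combined pure and placebo-inspired CGs" over the same length of waiting. Both CGs start the program after the wait, so no later comparison has an untreated arm.
- **Second hypothesis** (same section): the three groups follow similar courses in the "short (during eight weeks of active treatment) and long term (during the six months of follow-up" phases. Model 2 (Statistical analysis) accordingly has "time (pre-post or post-follow-up) as within-subjects factors".
- **Schedule** (Table 2, introduced as covering every instrument): the EDE-Q, "Assessment of eating disorders pathology during the past 28 days. 4 scales: eating concerns, weight concerns, restraint eating, shape concerns. 28 items", is at t1, t2 and t3. The EDE interview is at t1. The WBQ, "Questions to assess frequency of binge-eating episodes and regularity of eating behavior. 7 items", is weekly while patients wait and while they are treated.
- **During the wait** (Control groups): "Both CGs fill in a short questionnaire to assess core BED symptomatology (i.e. binge-eating episodes) and to monitor changes in mood".
- **Consent description** (Sample and recruitment): "diagnostic interview and questionnaires pre, post, and follow-up", with no mention of a mid-course assessment.

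**The concern.** The first hypothesis speaks of treatment outcomes in general, so it covers both primary outcomes. To test it, each outcome must be measured at the start and at week 4, in TG and in both CGs. For ED pathology the printed schedule has no week-4 measurement in TG.

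This matters because the four-week contrast is the only randomised evidence of efficacy against no treatment. Model 1 is an uncontrolled pre-post test pooled over all groups, and Model 2 compares groups that have all received the program. An analysis plan cannot supply values that were never collected, so this belongs to the assessment schedule.

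Two further timing questions arise from the same table: what counts as 'pre' for the CGs on the EDE-Q, and what supplies binge counts after the end of treatment.

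**Working it through.** **Inputs.** Time points come from Table 2. The text available does not define t1 to t3. The instruments placed there imply that t1 is pre-treatment (sociodemographic and expectancy items), t2 is the end of treatment (the system usability scale is given only there, and the final evaluation first appears there) and t3 is follow-up. The wait is four weeks (Control groups). Active treatment with pre and post diagnostics takes about 11 weeks, plus four in the CGs (Procedure). Allocation is 20:20:20.

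**Step 1. Needed against scheduled.**

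| Time point | Needed for | EDE-Q | WBQ |
|---|---|---|---|
| Start | both hypotheses | t1 | first weekly entry |
| Week 4 after randomisation | first hypothesis | not listed | weekly entry |
| End of treatment | second hypothesis, Models 1 and 2 | t2 | last weekly entry |
| Follow-up | second hypothesis, Model 2 | t3 | not listed |

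**Step 2. Does the week-4 gap depend on where t1 falls?** There are three possibilities for the CGs:

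- *t1 before the wait.* The CGs have a value at the start of the wait and none at its end. TG has none at treatment week 4.
- *t1 after the wait.* The CGs have a value at the end of the wait and none at its start. TG has none at treatment week 4.
- *t1 repeated, before and after.* The CGs have both values. TG still has none at treatment week 4.

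The four-week change in ED pathology cannot be compared between arms in any of the three cases. The EDE interview, listed at t1 only, does not help.

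**Step 3. Binge episodes at week 4.** The WBQ runs weekly in the CGs while they wait and in TG while it is treated, so weeks 1 to 4 are covered in every arm. The four-week contrast is available for this outcome.

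**Step 4. 'Pre' in the CGs on the EDE-Q.** If t1 precedes the wait and is the only pre-treatment value:

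- TG pre-post interval: about 11 weeks.
- CG pre-post interval: about 11 + 4 = 15 weeks, four of them untreated.
- Patients affected: 20 + 20 = 40 of 60, and 40/60 = 67%.

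Model 1, meant to test change during active treatment, would then include waiting-period change in two thirds of patients. Model 2's group-by-time term would compare intervals of unequal length. For binge episodes the difficulty does not arise, because the weekly WBQ gives the CGs a value at the end of the wait.

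**Step 5. Binge episodes after treatment.** Table 2 lists no WBQ after treatment, while Model 2 has a post-to-follow-up version and the second hypothesis covers six months of follow-up. The EDE-Q might yield a binge count, but Table 2 describes only its four scales, and its 28-day recall differs from a weekly count.

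**Step 6. Fit of the EDE-Q to week 4.** 4 × 7 = 28 days. A week-4 EDE-Q would look back over exactly the four weeks since randomisation, if treatment or waiting starts at randomisation.

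**The case against.** The strongest objection is that the schedule proper is Fig. 1, which was not available, and that t1 to t3 are undefined in the text. The sentence on the waiting period describes what the short questionnaire covers; it does not say that nothing else is collected. This stands as a caution. But Table 2 claims to list all instruments and gives each a time point. If Fig. 1 shows a week-4 EDE-Q, the two conflict and one must be corrected.

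Three stronger readings are tempting, and the documents do not support them.

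- *The main hypothesis is untestable.* It is not. The randomised contrast remains available for binge episodes, the outcome whose correlation underlies the power analysis.
- *Models 1 and 2 will credit waiting-period change to the program.* This follows only if t1 precedes the wait and serves as 'pre'. That is likely, because the diagnostic interviews sit at t1 and a BED diagnosis is needed for inclusion. But Procedure counts the pre-diagnostics inside the 11-week phase and adds the four waiting weeks separately, so 'pre' could be read as the start of treatment. Only the EDE-Q is affected either way.
- *Binge episodes have no baseline.* Table 2 lists no WBQ at t1, but the first weekly entry can serve as a near-baseline. This is minor.

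On follow-up, the Abstract describes the treatment as including three booster sessions, so 'treatment' in Table 2 might extend to them. But Procedure separates active treatment from follow-up, and a weekly schedule does not fit sessions at one, three and six months. The gap is real as printed, and it needs reconciling rather than assuming.

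**Conclusion.** The point holds in this form: on the schedule as printed, one of the two primary outcomes has no data for the only randomised comparison of treated with untreated patients. The four-week hypothesis can be tested on binge episodes and not on ED pathology. This does not depend on how t1 is defined; it rests on Table 2 being complete, as the article says it is.

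The secondary points carry conditions. The extra four untreated weeks in EDE-Q pre-post change, for 40 of 60 patients, apply if t1 precedes the wait and is used as 'pre'. The missing WBQ at follow-up applies if 'treatment' in Table 2 means the active phase, which is the more natural reading.

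**What to change.** 1. **Week 4.** Add the EDE-Q at week 4 after randomisation in all three arms. The cost is one extra 28-item online self-report and a minor amendment. Patients already past week 4 will lack the value, so delay loses data. If it is not added, restrict the four-week hypothesis to binge episodes. That costs no data collection, but gives up any randomised claim about ED pathology against waiting.
2. **Definition of 'pre'.** Define t1 to t3. If t1 precedes the wait, keep t1 as the randomisation baseline for the four-week contrast, and use the week-4 EDE-Q as the CGs' 'pre' value in Models 1 and 2.
3. **Follow-up.** Add the WBQ (seven items) at the follow-up assessments, so that post-to-follow-up change in binge episodes uses the same instrument and recall period as pre-post change.
4. **Consistency.** Reconcile Table 2 with Fig. 1. A separate WBQ at t1 would be helpful but is not essential; otherwise state that the first weekly entry is the baseline.
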